## Abstract

This protocol will outline the development of the CAMUS Intra- and Postoperative Risk and Difficulty Estimation Indices (IPRADES), a tool designed to predict perioperative outcomes and surgical complexity in major urological procedures. Its objective will be to enhance preoperative planning and risk stratification by systematically evaluating a range of patient-, organ-, and surgery-specific factors. The study will be conducted in three phases. Firstly, expert consensus will be established through a Delphi survey involving experienced high-volume surgeons to identify key parameters influencing surgical difficulty and complications. Secondly, data will be collected from the CAMUS Collaboration database and augmented with additional parameters from a prospective open cystectomy database. Thirdly, using this extensive dataset, a nomogram will be developed to evaluate the association between the identified parameters and postoperative complications, as well as to quantify their predictive values. Each parameter will be assigned a weighted significance, which will be integrated into the final risk prediction model. Statistical analyses will incorporate multivariable regression models to identify predictors of complications and mortality. The model’s performance will be evaluated through c-statistics, Hosmer-Lemeshow tests, and Brier scores, with internal validation performed via dataset splitting and bootstrap resampling. Additionally, the study will compare the predictive accuracy of universal versus procedure-specific models. The tool will not only account for patient and surgical factors, but also incorporate the influence of surgeon experience and learning curves on surgical outcomes. A web-based calculator will be developed to facilitate seamless integration into daily clinical practice, providing real-time risk assessments. Following validation, the CAMUS IPRADES tool will refine surgical planning, optimise resource allocation, and enhance patient counselling. By delivering data-driven risk assessments, it will further enable surgeon and institutional benchmarking, thereby contributing to education, training, and clinical research. Ultimately, this tool will play a pivotal role in advancing the quality and safety of urological surgeries.

## Introduction and hypotheses

1

Risk assessment is a cornerstone of surgical decision-making, influencing overall patient care profoundly. Accurate risk stratification not only determines patient suitability for surgical intervention, but also guides the selection of the most appropriate treatment modality. Furthermore, it plays a pivotal role in resource allocation, surgical planning, patient counselling, postoperative follow-up, and academic reporting.

Despite the availability of numerous risk indices, each existing system has notable limitations. Most contemporary models primarily emphasise patient characteristics and comorbidities to predict morbidity and mortality. For instance, the Surgical Apgar Score (SAS) serves as a predictor of major complications or mortality within 30 d after surgery. This score has been validated across various patient populations and is a recommended tool for objectively guiding postoperative care [1]. Other risk stratification tools widely adopted in general surgery include the Acute Physiology and Chronic Health Evaluation II [2], the American College of Surgeons National Surgical Quality Improvement Program [3], the Preoperative Mortality Predictor score [4], the Surgical Risk Preoperative Assessment System [5], the Surgical Outcome Risk Tool [6], and the Physiological and Operative Severity Score for the enumeration of Mortality and morbidity (POSSUM) [7]. Table 1 provides an overview of these tools. Among these, the POSSUM score is particularly comprehensive, integrating 18 parameters encompassing patient history, biochemical data, and radiological parameters. Notably, it distinguishes itself by incorporating operative findings into its predictions. While effective for benchmarking surgical quality, POSSUM was not originally designed to guide decisions regarding surgical candidacy.

**Table 1 t0005:** Current risk estimation tools in general surgery

System	Overview	Assessed variables
Physiological and Operative Severity Score for the enUmeration of Mortality and morbidity (POSSUM)	Estimates risk for operative morbidity and mortality. Has been designed specifically for audit purposes in the general surgical patient POSSUM contains 18 variables (12 variables concern the physiological score; six variables concern the operative score). The POSSUM uses values at the time of surgery, not admission, and should not be used for trauma patients.	*Physiological score*: Age, cardiac (eg medication, peripheral oedema), respiratory (eg, dyspnoea), blood pressure, heart rate, GCS, haemoglobin, white blood count, blood urea nitrogen, sodium, potassium, ECG *Operative score*: Operative severity (eg, minor, moderate, major, or major+), number of procedures, estimated blood loss, peritoneal soiling, presence of malignancy, mode of surgery (eg, elective, emergency)
Surgical Apgar Score (SAS)	SAS can predict 30-d major complications or death after surgery. It is a 10-point score based on three intraoperative parameters.	Variables: estimated amount of blood loss, lowest heart rate, and lowest mean arterial pressure
Acute Physiology and Chronic Health Evaluation (APACHE II) score	Estimates hospital mortality. APACHE II contains 13 variables (four vitals, three oxygenation, four chemistry, three haematology, age, and GCS), using the worst value for each physiological variable within the past 24 h. A calculator will convert an APACHE II score into percentage risk of mortality	Vitals: Temp, MAP, heart rate, and resp rate Oxygenation: FiO2, PaO2, arterial pH Chemistry: sodium, potassium, creatinine, acute renal failure Haematology: haematocrit, white blood count, severe organ system insufficiency or immunocompromised patient Age GCS
American College of Surgeons National Surgical Quality Improvement Program (ACS NSQIP)	ACS NSQIP is a nationally validated, risk-adjusted, outcome-based programme to measure and improve the quality of surgical care. It estimates the chance of an unfavourable outcome (such as a complication or death) after surgery.	Age group, gender, functional status (eg, partially dependent), emergency case, ASA class, steroid use for chronic condition, ascites or congestive heart failure within 30 d prior to surgery, systemic sepsis within 48 h prior to surgery, ventilator dependence, disseminated cancer diabetes, hypertension requiring medication, dyspnoea, current smoker within 1 yr, history of severe COPD, dialysis, acute renal failure, BMI
Preoperative Mortality Predictor score	Predicts the risk of perioperative mortality in general surgery patients, is a 30-point bedside score, and contains 14 variables.	Variables: Inpatient, sepsis, poor functional status (total assistance required for all daily activities), disseminated cancer, age, comorbidities (cardiac, pulmonary, renal, and liver), steroids for chronic condition, weight loss, bleeding disorder, obesity, and “do not resuscitate status”
Surgical Risk Preoperative Assessment System	Preoperative risk assessment of postoperative mortality, overall morbidity, and six complication clusters, achieved with as many as eight (out of 28) preoperative predictor variables.	Complication clusters: infection, cardiac/transfusion, pulmonary, venous thromboembolism, renal, and neurological Top eight preoperative predictor variables: ASA class, work relative value unit, systemic sepsis (within 48 h), inpatient/outpatient, primary surgeon speciality, age, functional health status before surgery, emergency operation Remaining 20 preoperative predictor variables: transfer status, body mass index category, ventilator dependency (within 48 h), open wound with or without infection, diabetes mellitus, cigarette smoker (within 1 yr), bleeding disorder requiring hospitalisation, disseminated cancer, transfusion of more than four units PRBCs (within 72 h), >10% loss of body weight (within 6 mo), steroid use for chronic condition, ascites (within 30 d), gender, race/ethnicity, acute renal failure (rising creatinine to >3 mg/dl within 24 h), blood pressure >140/90 mmHg or taking antihypertensive medicine, severe chronic obstructive pulmonary disease, dialysis or haemofiltration (within 2 wk), dyspnoea (within 30 d), and congestive heart failure (within 30 d)
Surgical Outcome Risk Tool	Estimates the risk of death within 30 d for specific operations. Nine variables are assessed.	Variables: main group (eg urinary system and male reproductive organs), subgroup (eg, ureter), procedure description (eg, unilateral replantation of ureter into bladder), severity (eg, major), ASA class, urgency (eg, elective), cancer, age, and “thoracic, gastrointestinal or vascular surgery”

ASA = American Society of Anesthesiologists; BMI = body mass index; COPD = chronic obstructive pulmonary disease; ECG = electrocardiogram; FiO2 = fraction of inspired oxygen; GCS = Glasgow Coma Scale; MAP = mean arterial pressure; PaO2 = arterial oxygen partial pressure; PRBC = packed red blood cell; resp = respiratory; Temp = temperature.

Despite the breadth of existing indices, no risk assessment tool tailored specifically for urological surgery exists. Instead, general indices such as the Charlson Comorbidity Index (CCI) and the American Society of Anesthesiologists (ASA) physical status classification system are often relied upon to assess baseline fitness for surgical management. Although these tools are associated with morbidity and mortality outcomes in urological procedures, these were not designed with urology-specific considerations in mind, limiting their clinical applicability. Recently, frailty indices such as the Comprehensive Geriatric Assessment have gained traction for preoperative assessments; however, their utility remains confined to select populations and does not comprehensively address the broader urological patient demographic.

Another critical limitation of the existing risk stratification tools is their reliance on preoperative variables while failing to integrate intraoperative findings. Intraoperative variables, which exert a significant influence on surgical complexity and postoperative outcomes, remain largely absent from most scoring systems. For example, nephrometry scores such as RENAL, PADUA, C-index, and the RPN classification [[8], [9], [10], [11]] consider preoperative imaging characteristics, but fail to incorporate intraoperative challenges that could alter surgical risk.

To address these shortcomings, there is an imperative need for a urology-specific risk assessment tool that will incorporate both preoperative parameters (eg, prostate size and tumour extent) and intraoperative variables (eg, fibrosis and extraprostatic tumour growth). Additionally, such a tool should account for surgical approach (eg, open vs minimally invasive and transperitoneal vs retroperitoneal) and patient-specific factors that may increase surgical complexity, such as prior neoadjuvant therapies, coagulopathies, or abdominal obesity (Table 2). By integrating these intraoperative considerations, risk stratification will be refined significantly, enhancing surgical planning as well as improving patient outcomes.

**Table 2 t0010:** Proposed CAMUS intra- and postoperative risk and difficulty estimation indices (IPRADES)

CAMUS IPRADES indices								
Non–organ-specific factors impacting surgical difficulty and risk for complication								
No.	Expected/known (preoperative) parameters				Unexpected/unknown (intraoperative) parameters			
	Parameter	Surgeon		Anaesthetist	Parameter	Surgeon		Anaesthetist
		Surgical difficulty (0 = no, 1 = yes)	Risk for complication (0 = no, 1 = yes)	Risk of complication (0 = no, 1 = yes)		Surgical difficulty (0 = no, 1 = yes)	Risk for complication (0 = no, 1 = yes)	Risk of complication (0 = no, 1 = yes)
1	Diabetes				Intraoperative fluids administered (ml)			
2	ASA classification				Estimated blood loss (ml)			
3	Timing of surgery (AM, PM)				Duration of operation (min)			
4	BMI (kg/m^2^)				ECG abnormalities			
5	Anticoagulant agents				Ventilation difficulties			
6	Elective vs emergency				General overall tissue quality			
7	Previous therapy: non–organ-specific (eg, radiation)				Ooziness/tissue vascularity			
8	Charlson Comorbidity Index				Scarred tissue			
9	Prior abdominal surgical history + type of surgery (eg, bowel resection vs cholecystectomy)				Adherent tissue			
10	Nutrition status (eg, albumin, weight loss, cachexia)				Identifiable planes			
11	Age				Vision			
12	Gender				Vessel injury			
13	Steroid use for chronic condition				Intraoperative blood transfusion			
14	Smoking status				–			
15	Further parameters to be proposed by Delphi experts				Further parameters to be proposed by Delphi experts			
Unexpected/unknown (immediate postoperative) parameters								

Parameter		Surgeon				Anaesthetist		
		Risk for complication (0 = no, 1 = yes)				Risk of complication (0 = no, 1 = yes)		

Acute kidney injury (ie, eGFR decrease by 10 ml/min)								
Significant demand for analgesia (ie, opioids >50 μg)								
Targeted organ-specific factors impacting surgical difficulty and risk for complication (organ-specific scoring system) shown in an exemplary way for laparoscopic/robotic radical prostatectomy								
	Expected/known (preoperative) parameters				Unexpected/unknown (intraoperative) parameters			
	Parameter	Surgeon			Parameter	Surgeon		
		Surgical difficulty (0 = no, 1 = yes)	Risk for complication 0 = no, 1 = yes)			Surgical difficulty (0 = no, 1 = yes)	Risk for complication (0 = no, 1 = yes)	
1	Prostatic size (cc) on MRI (eg, very small or very large)				Narrow bony pelvis			
2	Size of tumour on MRI (ie, maximal diameter in cm)				Extensive intrapelvic fat tissue			
3	Numbers of preoperative biopsies				Extensive prerectal fat tissue			
4	Numbers of biopsy cores taken				Fibrosed tissue at NVB (difficulty for application of Hem-o-loks/metal clips)			
5	Type of biopsy (TRUS vs TP)				Locally advanced/infiltrative tumour (pT3b/4)			
6	Gleason score (on biopsy)				Large/flaccid bladder			
7	Previous TUR-P				Scarred/stiff bladder (neck) tissue			
8	cT stage (DRE/MRI)				Accessory obturator vein			
9	Time between biopsy and surgery (eg, 1–3, 3–6, >6 wk)				Prominent periprostatic veins			
10	Previous radiation (including dosage, eg, LDR/HDR) ± ADT				Large DVC			
11	Inguinal hernia repair (laparoscopic vs open, with/without mesh)				Intra-abdominal adhesions			
12	BMI (obesity)				Osteophyte/bone spur (symphysis)			
13	–				Friable urethral tissue			
14	Further parameters to be proposed by Delphi experts				Further parameters to be proposed by Delphi experts			

ADT = androgen deprivation therapy; ASA = American Society of Anesthesiologists; BMI = body mass index; DRE = digital rectal examination; DVC = dorsal vascular complex; ECG = electrocardiogram; eGFR = estimated glomerular filtration rate; HDR = high-dose rate; IPRADES = Intra- and Postoperative Risk and Difficulty Estimation Indices; LDR = low-dose rate; MRI = magnetic resonance imaging; NVB = neurovascular bundle; TP = transperineal; TRUS = transrectal ultrasound; TUR-P = transurethral resection of the prostate.

CAMUS IPRADES indices: To create the CAMUS IPRADES indices, four different categories of proposed parameters will be incorporated in the risk and difficulty estimation tool: preoperative (known, expected) patient-specific parameters, intraoperative (unknown or unexpected) body/patient-specific parameters, preoperative targeted organ-specific parameters, and intraoperative targeted organ-specific parameters (eg, fibrosed periprostatic tissue).

## Design

2

### Study design

2.1

The primary aim of this study will be to formulate and achieve consensus on pertinent pre-, peri-, and postoperative risk factors and complicating conditions by incorporating expert opinions from diverse professional backgrounds. This process will ultimately lead to the creation of a risk and surgical difficulty index ranging from 0 (indicating no risk of complications and the lowest grade of difficulty relative to a standard procedure) to 100 (indicating death or procedure abandonment due to an excessively high level of difficulty). The authors acknowledge that no surgical procedure will be entirely devoid of risk; however, the adoption of a 0–100 scale will provide a pragmatic framework for risk stratification.

The Delphi method, a well-established technique for developing consensus-based best practice guidelines [[12], [13], [14], [15], [16], [17], [18], [19]], will serve as the foundation of this study. This scientifically validated group communication process will encompass 11 structures [13,20], which will be delineated in detail within the study methodology (see Fig. 1A).

**Fig. 1 f0005:**
[figure not shown]

[figure not shown]
(A) The 11 steps of the Delphi method to achieve global consensus on perioperative risk and difficult estimation. (B) Overview of organ- and approach specific interventions for which targeted organ-specific factors impacting surgical difficulty and risk for complication (organ-specific scoring system) will be defined. PCNL = percutaneous nephrolithotomy; PLND = pelvic lymph node dissection; RPLND = retroperitoneal lymph node dissection; TUR-B = transurethral resection of the bladder; TUR-P = transurethral resection of the prostate; URS = ureteroscopy.

A summary of the Delphi study approach is presented in Table 3, encompassing key aspects such as method selection, expert participant nomination, invitation and follow-up protocols, sample size considerations, response rate, consensus definition, and selection of the steering committee. Expert participants will include high-volume local and international urologists, general surgeons, and consultant anaesthetists, with a particular emphasis on those specialising in urological critical care. These participants will be identified through the CAMUS Collaboration databases and trial coordinators, and will be contacted via e-mail. All invited experts will be encouraged to complete all Delphi rounds. Round 1 will remain open for 4 wk, with weekly reminders issued to ensure engagement. The study will aim for a minimum sample size of 50 participants, comprising 20 urologists, ten general surgeons, and 20 anaesthetists. In cases of participant withdrawal, follow-up inquiries will be conducted to ascertain the reasons for discontinuation.

**Table 3 t0015:** Study approach

#	Section	Question
1	Delphi method	Eleven steps of the Delphi study (see Fig. 1).
2	Selection of nominated expert participants	Local and international high-volume urologists, general surgeons, and consultant anaesthetists are invited to complete the survey. Primarily urological experienced critical care specialists will be targeted.
3	Invitations and reminders to Delphi participants	Participant experts will be contacted via e-mail (obtained via CAMUS databases and trial coordinators). All participants will be invited to complete all Delphi rounds. Round 1 will be closed after 4 wk. Reminders will be sent every 7 d.
4	Sample size and response rate for the Delphi study	Minimum sample size of 50 participants (20 urologists, ten general surgeons, 20 anaesthetists) will be targeted. In case of withdrawal, participants will be contacted to identify the reason for withdrawal.
5	Defining and achieving final consensus	Consensus will be defined, a priori, as majority agreement (≥75%) of participant response. If consensus is not reached, then subsequent Delphi rounds (minimum of two, maximum of five) will be performed under the guidance of the steering committee.
6	Steering committee selection	Committee members will be selected primarily from our team of investigators, as well as several highly experienced specialists (urologists, general surgeons, anaesthetists, methodologists, and radiologists [for assessment/discussion of radiologically evident risk factors, eg, clinical staging]) in surgical reporting.

Consensus will be defined, a priori, as a majority agreement of ≥75% among participants [15,21,22]. If consensus is not achieved, additional Delphi rounds (ranging from a minimum of two to a maximum of five) will be conducted under the guidance of the steering committee. This committee will be composed primarily of study investigators and highly experienced specialists, including urologists, general surgeons, anaesthetists, radiologists (for the assessment of radiological risk factors such as clinical staging), and methodologists specialising in surgical reporting.

In the initial phase, the most common uro-oncological procedures will be evaluated to establish organ-specific correlations with surgical difficulty and peri- and postoperative risk profiles (see Fig. 1B). These procedures will include standard radical prostatectomy (RP), transperitoneal partial nephrectomy (PN), nephroureterectomy/nephrectomy, and radical cystectomy (RC; both male and female) with urinary diversion, encompassing ileal conduit and orthotopic neobladder formation.

Should these indices demonstrate clinical applicability through prospective validation, further evaluations of additional major and minor interventions will be undertaken in subsequent Delphi processes (Fig. 1B).

Ethics approval for this study has been granted through the Research Governance and Quality Assurance Team at Epworth HealthCare (Epworth ID: EH2021-708). Furthermore, the study has been registered with ClinicalTrials.gov PRS (NCT04976946) as of August 12, 2021.

### Study aims

2.2

The final Delphi document will aim to synthesise expert consensus and provide guidance in areas of on-going debate within the field of urological surgery. Its findings will be of significant relevance and potential applicability to other surgical disciplines, ensuring the dissemination of optimised guidance to clinicians and patients alike. Ultimately, these position statements will be incorporated into internationally recognised guidelines issued by urological associations.

The primary objective of this study will be to develop a peri- and intraoperative risk prediction index and scoring system to estimate and quantify surgical difficulty, as well as to construct targeted, organ-specific scoring systems based on pre- and intraoperative factors. Similar to the existing renal scoring systems [8,9,11], the objective will be to establish a checklist-based framework to assist in surgical planning, case selection, and stratification of procedures based on their suitability for teaching purposes (see Fig. 1B).

The main objectives of the study will be the following (Table 4):1.To predict intraoperative (during intervention), perioperative (in-hospital period), and postoperative (within a defined period after intervention) outcomes by considering both pre- and intraoperative factors2.To predict intra-, peri-, and postoperative outcomes based solely on preoperative factors, thereby optimising resource allocation and enabling the identification of appropriate teaching cases prior to surgery3.To define surgical difficulty as an independent metric for the comparative analysis of intra-, peri-, and postoperative outcomes across surgeons and procedures. This will necessitate the delineation of parameters contributing to surgical complexity from both an anaesthetic and a surgical perspective. Consideration will be given to anaesthetic and surgical case volume, frequency of procedures over a given timeframe, and individual learning curves, as these factors will influence both case complexity and the risk of complications4.To develop multiple indices for surgical risk and difficulty estimation, which will be calculated both preoperatively and immediately postoperatively

**Table 4 t0020:** Study aims

#	Aim
1	To predict intra-, peri-, and postoperative outcomes by considering pre- and intraoperative factors
2	To predict intra-, peri-, and postoperative outcomes by considering preoperative factors only, to optimise the allocation of critical care resources or defining teaching-appropriate cases before surgery starts
3	To determine surgical difficulty as a separate matter to judge surgical performance by improving the comparison of intra- and postoperative outcomes between surgeons and between different interventions
4	To define parameters that make certain operations (and approaches) for anaesthetists and urologists more difficult
5	To create several indices (surgical risk and difficulty estimation) that are calculated before and immediately after surgery

The surgical difficulty and risk estimation tool will integrate five categories of patient-specific parameters (Table 2):1.Preoperative (known, expected) patient-specific characteristics and conditions (eg, body mass index [BMI], ASA score, sex, prior abdominal surgery, and comorbidities)2.Intraoperative (unknown or unexpected) body/patient-specific characteristics and conditions (eg, bleeding tendency, restricted operative space due to a narrow bony pelvis, or extensive adhesions)3.Preoperative targeted organ-specific parameters (eg, tumour size and location, organ anatomy and morphology, or a history of prior interventions on the targeted organ such as biopsies or transurethral resection of the prostate preceding prostatectomy)4.Intraoperative targeted organ-specific parameters (eg, fibrosed periprostatic tissue or tumour extension beyond the targeted organ).5.Unexpected/unknown postoperative conditions prior to discharge or within 24 h (eg, acute kidney injury, quantified by a decrease in glomerular filtration rate [ml/min])

Surgical and anaesthetic parameters will be evaluated independently to account for the influence of case volume and individual learning curves on surgical complexity and risk. The key variables will include the total case volume, frequency of procedures performed within a defined period, and complexity of prior cases. Additionally, institutional case load will be considered when estimating perioperative morbidity risk (eg, in tertiary referral centres).

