It is essential to differentiate between the absolute and relative risks within this framework. Certain patient-specific factors, such as prior radiation therapy, inherently elevate the absolute risk and case difficulty. However, a highly experienced surgeon (eg, one with >500 completed cases) can mitigate these challenges in relative terms. Consequently, the calculated risk and difficulty index for a given case may be adjusted downward when performed by an experienced surgeon, incorporating their proficiency into the assessment model.

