### Surgeon risk adjustment

4.2

Given that the surgical difficulty and peri- and postoperative complication risks estimated by the calculator may not encompass every potential comorbidity, an ad hoc provision will be introduced, allowing surgeons to adjust the estimated risks reasonably. Recognising the inherent uncertainty (confidence interval) around the calculated risks, clinicians will be permitted to modify the risk and difficulty estimates within the confidence interval for each outcome measure. Surgeons will be allowed to increase the estimated risks by up to 30 points (on a scale of 0–100) if deemed necessary.

To evaluate the relative value of generic versus surgery-specific risk models, surgery-specific models will be developed for the three most common surgical specialities in the database (RC, RP, and PN). The C-indices, HL analyses, and Brier scores for the generic model will then be compared against those of the surgery-specific models applied to the same patient subgroups defined by subspeciality.

By creating a single model applicable across a wide range of surgical outcomes and difficulties, the aim is to streamline the preoperative risk assessment process. However, it is acknowledged that, in certain circumstances, surgery-specific models may yield more precise risk estimates. This suggests that the optimal strategy may involve a balanced approach, incorporating the simplicity of a generic model while maintaining the accuracy of speciality-specific models where appropriate.

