### Discussion

5.1

The ultimate goal of risk prediction is to raise awareness among surgeons regarding challenging perioperative conditions, thereby preventing negligence and reducing the risk of complications. Additionally, it helps patients and their families better understand the implications of complex surgical procedures. By estimating individual risks and difficulties for each patient, this approach facilitates stratification of surgeries, helping in determining which procedures may be suitable for training or teaching purposes.

Although clinical judgement based on pre- and intraoperative factors is crucial, it alone is insufficient for predicting adverse outcomes following surgery [27]. Consequently, various perioperative risk prediction tools, such as risk stratification calculators, have been developed and validated to identify high-risk patients [28,29]. Emerging evidence continues to demonstrate that proper risk assessment improves patient outcomes significantly. These tools rely on multiple patient-specific variables and mathematical models calibrated using large datasets, providing a quantitative assessment of risk.

These variables can also be used to compare expected and observed outcomes across different surgeons, allowing for individual performance tracking as well as comparisons between various centres and regions. However, despite their potential, most of these tools are not yet implemented routinely, as none meet all the criteria for an ideal scoring system.

All contributing factors should ultimately be synthesised into a comprehensive scoring system comprising both a “targeted organ-specific subscore”, which reflects preoperative parameters, and an integrated score that combines pre- and intraoperative considerations. This consolidated scoring system would serve as a vital component of an overarching risk assessment tool.

The surgical difficulty and risk estimation framework should encompass five distinct categories of patient-specific parameters: (1) preoperative patient- or body-specific characteristics and conditions (known and expected), (2) intraoperative patient- or body-specific factors (unknown or unexpected), (3) preoperative organ-specific parameters (known and expected), (4) intraoperative organ-specific parameters (unknown or unexpected), and (5) postoperative conditions (unknown or unexpected) observed before discharge or within the first 24 h.

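### Surgical difficulty is meant for judging surgeons, but as described it draws on operator-dependent quantities, which would pull surgeon comparisons towards no difference

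*Protocol article*

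**What the plan says.** **Purpose.** Section 2.2 makes difficulty a metric for comparing outcomes across surgeons and procedures (objective 3). Table 4, aim 3 is explicit: "To determine surgical difficulty as a separate matter to judge surgical performance by improving the comparison of intra- and postoperative outcomes between surgeons". Section 5.1 adds: "These variables can also be used to compare expected and observed outcomes across different surgeons, allowing for individual performance tracking".

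**Inputs.**
- Table 2 proposes intraoperative parameters to be rated for both difficulty and complication risk. They include "Vessel injury", "Intraoperative blood transfusion", estimated blood loss and duration of operation.
- Section 4.1 names duration, blood loss and transfusion, use of haemostatic agents and the surgeon's judgement as the primary outcome measures for difficulty.
- Section 3.4 has the surgeon update the risk and difficulty estimates straight after the operation.
- Objective 3 itself brings in case volume and learning curves. Section 3.6 adds that "the calculated risk and difficulty index for a given case may be adjusted downward when performed by an experienced surgeon".
- Section 4.2 lets clinicians modify risk and difficulty estimates: "Surgeons will be allowed to increase the estimated risks by up to 30 points".

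**Alternative already foreseen.** Sections 2.2 and 3.6 foresee a preoperative-only prediction or index. They link it to decision-making, critical care resources and teaching cases, not to comparing surgeons.

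**The concern.** An expected value used to compare operators should describe the case the surgeon was given. Vessel injury, bleeding and a long operation are partly what the surgeon did with that case, so they lie on the path from operator to outcome. Experience is a characteristic of the operator. A manual uplift is under the operator's control. All of these can be valid inputs for predicting one patient's course after surgery, but that does not make them valid for case-mix adjustment.

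If they enter the expected value, a surgeon who causes bleeding is credited with a harder case. A surgeon whose results are poor through inexperience is measured against a standard already relaxed for inexperience. The comparison then tends to reassure about the surgeons it should detect.

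**Working it through.** The plan gives no figure for this point. The check is first textual, then illustrative.

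**Step 1: which index could serve aim 3?** Section 3.6 leaves three possibilities open.
- *Preoperative index:* free of intraoperative inputs, but given other purposes.
- *Combined index:* contains intraoperative parameters and is meant for broader objectives.
- *Separate difficulty index:* judged against the outcomes in section 4.1, which depend on the operator.

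The two candidates not reserved for other purposes therefore both draw on operator-dependent quantities. Aim 3 also compares intraoperative outcomes, so blood loss or duration could stand on both sides of the comparison.

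**Step 2: simulation of observed/expected (O/E).** All parameters are assumptions; none comes from the article. There are 40 surgeons with 4,000 cases each, 10 of them poor performers, and preoperative case mix x is distributed alike in both groups.
- Mishap: log-odds = −2.2 + 0.5x + 1.2·poor
- Complication: log-odds = −1.5 + 0.6x + 1.8·mishap + b·poor

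With b = 0 all harm runs through the mishap. With b = 0.3 some bypasses it. The table shows the O/E of poor surgeons divided by the O/E of the others.

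| Expected value from | b = 0 | b = 0.3 |
|---|---|---|
| (ratio of raw complication rates) | 1.26 | 1.48 |
| Preoperative case mix | 1.27 | 1.49 |
| plus mishap | 1.00 | 1.18 |
| plus mishap and experience | 1.00 | 1.13 |

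The preoperative model recovers the true excess. Adding the mishap removes it wholly or in part.

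**Step 3: a second model.** Assumptions: 30% complications, a true odds ratio of 1.6 for the poor group, a continuous mediator with coefficient 0.6, and expected values fitted on the other surgeons. Preoperative adjustment gives an O/E of about 1.31. With the mediator included, O/E is 1.32, 1.14, 1.07 and 1.00 when 0%, 50%, 75% and 100% of the effect passes through it. If none of the effect is mediated, nothing is masked.

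**Step 4: manual uplift.** This step assumes that one index point equals one percentage point of risk and that the uplift is applied to every patient. For an exactly average surgeon with true risk p and uplift d, O/E = p/(p + d).
- p = 0.25, d = 0.10: 0.25/0.35 = 0.71
- p = 0.25, d = 0.30: 0.25/0.55 = 0.45
- For p from 0.15 to 0.40: 0.60 to 0.80 with d = 0.10, and 0.33 to 0.57 with d = 0.30

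**Step 5: what if every intraoperative item is dropped?** Take an exactly average surgeon group whose patients have worse anatomy, visible only at operation. Assume 30% complications, a shift of 0.25 to 0.75 SD and a log-odds ratio of 0.4 to 0.6 per SD. Preoperative-only O/E is falsely about 1.08 to 1.31; with anatomy included it is 0.99 to 1.01. Blanket exclusion therefore has its own bias.

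**The case against.** **Nothing is biased yet.** The statistical sections plan no surgeon contrast, ranking or O/E ratio, and the observed-versus-expected sentence sits in the Discussion as a possible use. This stands. A reader might infer that objective 3 will be answered wrongly, but the article fixes no estimate of which that could be said. It does fix the purpose of the metric and describes what goes into it, and those two do not fit together.

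**The inputs are open.** Table 2 lists proposals for the Delphi panel, and the number of indices is undecided. This also stands, so the index cannot be said to contain vessel injury. But the panel is asked whether an item affects difficulty or risk, not whether it is attributable to the operator. The section 4.1 difficulty outcomes are named in the plan, and objective 3 already calls for experience to be considered.

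**Experience has other uses.** Section 3.6 gives the experience strata two purposes: estimating how experience reduces difficulty and risk, and judging suitability for teaching. A lower expected value also makes the standard stricter for experts. True, but a stricter standard for experts and a laxer one for novices is exactly how the difference between them shrinks.

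**The uplift is for missed comorbidity.** Section 4.2 gives that reason and also confines changes to the confidence interval. That uplifted values would enter a surgeon comparison is only an inference; no text sends them there, and none keeps them out.

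**Some intraoperative findings are case mix.** Adhesions and a narrow pelvis belong to the patient. This stands and narrows the remedy.

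**Conclusion.** The concern holds as a mismatch between stated purpose and described inputs. If an index built as described supplies the expected value, differences between surgeons are biased towards no difference. The size depends on how much of the surgeon's effect passes through the adjusted quantities: none of the excess is masked at 0% mediation, all of it at 100%. The simulated figures show direction and plausible scale under assumed parameters; they do not estimate the bias in the CAMUS data.

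Two stronger readings are not supported. One is that poor performance is adjusted away altogether, which requires full mediation. The other is that surgeons can certainly improve their O/E by entering a higher risk. That requires uplifted values to be used in the comparison, which the article does not say, and the figures in step 4 hold only if index points are percentage points of risk. Section 2.1 describes the 0–100 scale as a combined risk and difficulty index and makes no such equation.

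Prediction of an individual patient's course from pre- and intraoperative factors (aim 1) is unaffected.

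**What to change.** State in sections 2.2 and 3.6 that any comparison of surgeons, centres or regions takes its expected value, as the primary adjustment, from preoperative patient- and organ-specific factors plus procedure. Exclude from it:
- operator-dependent intraoperative events (vessel injury, blood loss, duration, transfusion);
- immediate postoperative conditions;
- surgeon, anaesthetist or centre experience or volume;
- any manual adjustment.

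Allow patient anatomy first seen at operation, such as adhesions or a narrow pelvis, to be added, at least as a sensitivity analysis. Keep the full index for individual prediction. In section 4.2, also reconcile the confidence-interval limit with the 30-point limit.

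The cost is wording, since a preoperative-only prediction is already an aim and uses the same data. The downside is a choice between two imperfections: leaving intraoperative anatomy out keeps some case-mix confounding, which can penalise surgeons who take harder cases, while including it depends on the operator's own, partly subjective recording. Reporting both analyses shows how much it matters.
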